### Statistical analysis

The primary analysis will be an available case analysis following intention to treat principles. We will use mixed effect models as appropriate to the outcome, with fixed effects for the intervention, baseline level of outcome and centre, and random effects for therapy groups. For continuous outcomes we will use Stata’s *xtmixed* command, *xtmepoisson* for count outcomes, and *gllamm* for ordinal outcomes. We will assess whether there is a clustering effect due to therapist or instructor (some therapists or instructors will lead two groups), but will not take this element of clustering into account in the analysis.

We will use sensitivity analyses to explore the impact of any missing data, including extreme scenario sensitivity analyses, for example that those who are lost to follow up would have no improvement as result of any intervention. If there are sufficient missing values to warrant its use, we will use multiple imputation following an exploration of patterns of missingness. We expect to use the MAR (missing at random) assumption in this imputation. In case group dropout (as opposed to study dropout) is higher in one condition compared to the other, we will conduct a simple complier-average causal analysis with compliers defined by the active intervention. Compliance will be defined as attendance of five or more sessions of BPT.

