### Proposed sample size

A 20% reduction in the PANSS negative scale has been defined as clinically significant [25], which we would anticipate to be a difference of approximately 3 points given the eligibility criteria. To detect a difference of 3 points, with a standard deviation of 5, at alpha = 5%, and a power of 90%, 58 patients are required in each arm. Assuming an intra-cluster correlation coefficient for treatment group of 0.1, and 7 patients per group with analysable data at the end of treatment gives an inflation factor of 1.6 [24] leading to a required sample size of 93 in each arm. At six months we expect a loss to follow-up of 31%, resulting in 5.5 individuals per group on average and an inflation factor of 1.45; recruiting 128 per arm (16 groups of 8 in each arm) leaves 88 per arm at 6 months and 91% power to detect a difference of 3 points at this time point (see Figure 1). One hundred and twenty eight patients per arm, i.e. 16 groups of approximately 8 patients in each arm will give 94% power for the end of treatment analysis. We do not expect to recruit and allocate exactly eight individuals within each group but the variation in group size will be small and will not materially affect the power of the trial.

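### The primary mixed model tests treatment against only 32 therapy groups with no REML fit or small-sample reference stated; under z inference the type I error would be about 5.5-9%, not 5%

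*Protocol article*

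**What the plan says.** The section Statistical analysis sets the model as mixed, "with fixed effects for the intervention, baseline level of outcome and centre, and random effects for therapy groups", and names one Stata command each for continuous, count and ordinal outcomes. It does not say whether the continuous model is fitted by ML or REML, which reference distribution is used, or whether degrees of freedom are corrected.

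The section Proposed sample size plans 16 groups of about 8 patients in each arm, "Assuming an intra-cluster correlation coefficient for treatment group of 0.1". For the primary time point it states that "7 patients per group with analysable data at the end of treatment gives an inflation factor of 1.6", and that the planned numbers "will give 94% power for the end of treatment analysis". For 6 months it claims "91% power to detect a difference of 3 points at this time point", with 88 patients per arm and an inflation factor of 1.45. The section Outcome measures places the primary hypothesis at end of treatment.

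**The concern.** Each therapy group belongs wholly to one arm, so the treatment effect is a between-group contrast. Its standard error depends on a between-group variance estimated from 32 groups, and the centre terms use up some of that information. With so few groups, a z reference treats the estimated variance as known, and ML also tends to underestimate it. The primary test would then reject too often when there is no effect, and the primary interval would be too short.

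The design effect in the sample size calculation enlarges the variance for clustering, but it makes no allowance for how few groups there are from which to estimate that variance. This would be so even if every therapist led one group only, so it is separate from the plan's decision not to model therapist clustering.

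**Working it through.** **Inputs from Proposed sample size:** difference 3, SD 5, alpha 5% (sidedness not stated; two-sided reproduces the plan), ICC 0.1, 16 groups per arm, 7 analysable patients per group at end of treatment and 5.5 at 6 months. **Assumed:** number of centres, estimator (ML or REML) and reference distribution (z or t).

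**1. The plan's own figures.**
- Unclustered n = 2 × (1.960 + 1.282)² × 5² / 3² = 58.4 per arm; the plan states "58 patients are required in each arm".
- Design effects: 1 + (7 − 1) × 0.1 = 1.6 and 1 + (5.5 − 1) × 0.1 = 1.45. Then 58 × 1.6 = 92.8, i.e. 93.
- End of treatment: 16 × 7 = 112 per arm; 112 / 1.6 = 70 effective. SE = 5 × √(2/70) = 0.845; 3 / 0.845 = 3.55; power = Φ(3.55 − 1.96) = 94.4% (stated 94%).
- Six months: 88 / 1.45 = 60.7 effective. SE = 5 × √(2/60.7) = 0.908; 3 / 0.908 = 3.305; power = Φ(3.305 − 1.96) = 91.1% (stated 91%).

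Both figures reproduce.

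**2. Power with group-level df.** With 32 − 2 = 30 df the critical value is 2.04. The non-central t with the same non-centrality gives 93.0% at end of treatment and 89.2% at 6 months. With 25-28 df (several centres), the 6-month figure is 88.8-89.1%.

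**3. Type I error of an uncorrected z test, analytic.** If the statistic follows t but is compared with 1.96, P(|t| > 1.96) is 5.9% on 30 df and 6.1% on 25 df.

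**4. Type I error by simulation.** Random-intercept data with no treatment effect, 32 groups, ICC 0.1, binomial group sizes (mean 7 or 5.5 of 8), a baseline covariate unrelated to outcome, and centre as a fixed effect. There were 10,000-12,000 data sets per scenario (simulation error about 0.2 points). The t column uses 32 minus arm and centre parameters. Ranges cover both time points.

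| Centres (assumed) | REML, z | REML, t | ML, z | ML, t |
|---|---|---|---|---|
| 1 | 5.7-5.9% | 4.8-5.0% | 6.5-6.7% | 5.5-5.7% |
| 2 | 5.7-5.9% | 4.8-4.9% | 6.9-7.1% | 5.8-6.0% |
| 4 | 5.7-6.7% | 4.8-5.6% | 7.8-9.1% | 6.6-7.7% |
| 8 | 6.2-6.4% | 4.9-5.2% | 10.1% | 8.4-8.5% |

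REML with t brings the error close to 5%. ML with t does not, so both parts of the correction are needed. With 4 centres, a true ICC of 0 gives 4.3-4.5% (REML, z) and 5.0-5.5% (ML, z). An ICC of 0.05 gives 5.6-5.7% and 7.0-7.3%.

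**5. Power under each choice, simulated at ICC 0.1 with 1 to 4 centres.** At 6 months, z gives 89.5-90.6% (REML) or 91.1-92.2% (ML), and REML with t gives 87.6-88.9%. At end of treatment, REML with t gives 92.3-92.8%. The simulated t figures sit slightly below step 2, which ignores unequal group sizes and the df spent on centres.

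**6. Baseline adjustment.** Suppose SD 5 is unadjusted and a baseline correlation r reduces the within-group variance only. The variance of a group mean is then 2.5 + 22.5 × (1 − r²) / m. With t on 30 df, 6-month power is 90.8% at r = 0.3 and 93.6% at r = 0.5. The values of r are assumptions.

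**The case against.** The strongest reply is that the article is only silent. Estimator and reference distribution are commonly left to an analysis plan, which may exist and settle them. Nothing in the text commits the analysis to ML or to z, and the behaviour of the command by default is not in the document. This stands, and it is why the type I error figures are conditional. The recommendation survives because the model, the command and the number of groups are fixed here, and run without a small-sample correction they give too short an interval.

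A reader might infer that the power figures prove a z-based analysis. They do not. A t reference on individual-level df gives 94.1-94.2% and 90.6-90.8%, which round to the same 94% and 91%. A planning approximation also does not bind the later test. What the figures do show is that group-level df were not allowed for.

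A reader might also infer that the trial suffers both an inflated type I error and 89% power. These belong to different tests and cannot be charged together. Nor is 91% an arithmetic error: it reproduces, 6 months is not the primary time point, and a modest baseline correlation could make good the loss. Baseline adjustment does not, however, repair the type I error of a z test.

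**Conclusion.** The point holds in conditional form and is modest in size. At the planning ICC of 0.1, with 32 groups and 1 to 4 centres, z inference would give a type I error of about 5.5-6.5% under REML and about 6.5-9% under ML, against the nominal 5%. The upper end needs ML and several centres. The inflation largely disappears if the true ICC is near zero, but the plan itself assumes 0.1.

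Under a valid group-level test, with no credit for baseline adjustment, power is about 93% at the primary time point, above the 90% target, and about 89% at 6 months, just below it. The documents do not support calling the trial underpowered or the stated powers miscalculated.

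**What to change.** State that continuous outcomes are fitted by REML. Base the test and confidence interval for the intervention on Kenward-Roger or Satterthwaite degrees of freedom, or on t with df equal to the number of groups minus the arm and centre parameters.

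In Proposed sample size, add that 94% and 91% do not allow for the limited group-level df, and that with such a test, before any gain from baseline adjustment, power is about 93% at end of treatment and 89% at 6 months.

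The cost is a few sentences. Compared with REML and z, intervals widen by about 4% (2.04 / 1.96 = 1.04); compared with ML and z, by somewhat more. Neither the sample size nor the conduct of the trial changes.

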## Methods

### Study Design

In a randomised controlled trial, schizophrenia patients with negative symptoms will be randomly allocated to groups for BPT or Pilates as an active control. Both conditions are in addition to treatment as usual and will be delivered in groups of about 8 patients each. There will be 3 data collection points; before treatment, after the 10 week treatment period, and after a 6 month follow-up period. Each therapist in either condition will run a maximum of two groups, and in each group they will be assisted by a co-facilitator. The trial cannot be fully “blind” because clinicians and patients cannot be masked towards the allocation of the patients to the experimental or control group. However, researchers who conduct the outcome assessments will be masked to the allocation of patients, and the eligibility and baseline assessments will occur pre-randomisation. All the analysis will be conducted blind to the participant allocation.

Originally, the plan was to randomise 16 patients at a time in each site, eight to intervention and eight to control, but this was changed for logistic reasons. We will now recruit a larger number, i.e. up to 20 patients in one batch, to ensure we have a sufficient number of participants randomised to cover any dropout between the eligibility and baseline assessment phases. After the baseline assessments, participants will be randomly allocated to the intervention or control group in batches using randomly permuted blocks of 4 and 6, starting each batch at the start of a new block to preserve balance. Conducting the randomisation in this manner allows us to randomise all the participants in one batch either at the same time or over two time points, allowing the research team more time to finalise the logistics involved with getting all the participants to the groups at the correct times.

BPT and Pilates groups will both run for 10 weeks. After the 10 week intervention period and after a further 6 month follow-up patients will be interviewed by the researchers and outcomes will be assessed. These assessments will be conducted either on NHS sites or in the community, ideally in the same location as the original assessments.

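### The plan commits in advance to leaving therapist clustering out of the analysis, so the standard error is too small to the extent that groups led by the same therapist are correlated

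*Protocol article*

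**What the plan says.** The Statistical analysis section of the protocol article specifies mixed models with fixed effects for intervention, baseline level and centre, and a random effect for therapy group. It says that clustering by therapist or instructor will be assessed, and then that "some therapists or instructors will lead two groups), but will not take this element of clustering into account in the analysis". No outcome of the assessment would change this.

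Under Study Design: "Each therapist in either condition will run a maximum of two groups". Planned interventions repeats the limit for both conditions. It also says that BPT is led by accredited dance-movement psychotherapists and Pilates by qualified instructors, so each leader works in one arm only.

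The Proposed sample size section allows for clustering by group: "Assuming an intra-cluster correlation coefficient for treatment group of 0.1, and 7 patients per group with analysable data at the end of treatment". It gives no correlation between groups that share a therapist and no number of therapists expected to lead two groups.

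**The concern.** Two groups run by the same person may do similarly well or badly. The planned model counts them as two independent clusters. Because therapists are nested in arm, any such correlation goes into the variance of the arm comparison and does not cancel between arms. The fixed effect for centre does not cure this: it removes what both arms share within a centre, while differences between therapists in different arms stay in the treatment contrast.

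If the correlation is positive, the confidence interval for the primary effect is too narrow and the test rejects too often under the null. The assessment offers no protection, since the plan has already decided not to act on it. The Background section itself lists reliance on a single BPT therapist among the main limitations of the exploratory trial, so variation between therapists is part of what this trial has to allow for.

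**Working it through.** **Inputs from Proposed sample size.** Difference 3 points; SD 5; alpha 5% (taken as two-sided, which reproduces the figures); same-group correlation 0.1; 16 groups per arm; 7 analysable patients per group at end of treatment and 5.5 at six months, that is 16 × 7 = 112 and 88 per arm.

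**The plan's own figures.**
- Unclustered n per arm = 2 × (1.96 + 1.28)² × 5² / 3² ≈ 58.4, given as 58.
- Design effect = 1 + (m − 1) × 0.1. For m = 7 it is 1.6, and 58 × 1.6 = 92.8, given as 93. For m = 5.5 it is 1.45.
- Power = Φ(0.6 × √(n_eff / 2) − 1.96), where 0.6 = 3/5 and n_eff is n per arm divided by the design effect.
- End of treatment: n_eff = 112 / 1.6 = 70, power 94.4%. Six months: n_eff = 88 / 1.45 = 60.7, power 91.1%.

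Both stated powers reproduce, with groups taken as independent.

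**Adding the shared therapist.** Let f be the share of groups led by a two-group therapist, and r the correlation between patients in different groups of the same therapist. Neither is in the document, so both are assumptions. The same-group correlation stays at 0.1, which bounds r between 0 and 0.1. A patient whose therapist leads two groups is also correlated r with m patients in the other group, so on average

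DE = 1 + (m − 1) × 0.1 + f × m × r.

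With DE₀ the planned value (1.6 or 1.45), the standard error is too small by a factor √(DE / DE₀), and the real two-sided type I error of the planned test is 2 × [1 − Φ(1.96 / √(DE / DE₀))]. Example for f = 1, r = 0.05 at end of treatment: DE = 1.6 + 7 × 0.05 = 1.95; factor √(1.95 / 1.6) = 1.10; type I error 7.6%.

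Power below is that of a test with the correct standard error, before any gain from baseline adjustment.

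| f | r | DE, end of treatment | SE too small by factor | Type I error | Power, end of treatment | Power, six months |
|---|---|---|---|---|---|---|
| 0 | any | 1.60 | 1.00 | 5.0% | 94.4% | 91.1% |
| 0.5 | 0.02 | 1.67 | 1.02 | 5.5% | 93.5% | 90.0% |
| 0.5 | 0.05 | 1.775 | 1.05 | 6.3% | 92.1% | 88.5% |
| 0.5 | 0.10 | 1.95 | 1.10 | 7.6% | 89.5% | 85.8% |
| 1 | 0.02 | 1.74 | 1.04 | 6.0% | 92.6% | 89.0% |
| 1 | 0.05 | 1.95 | 1.10 | 7.6% | 89.5% | 85.8% |
| 1 | 0.10 | 2.30 | 1.20 | 10.2% | 84.2% | 80.4% |

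The row f = 0 shows why one-group therapists do no harm: therapist and group are then the same cluster. A simulation of group means at end of treatment, analysed as if groups were independent and with a t reference, agrees: type I error 5.0% with r = 0, 6.2% at f = 0.5 and r = 0.05, 7.6% at f = 1 and r = 0.05, and 10.6% at f = 1 and r = 0.10.

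**The case against.** The strongest reply is that the effect is probably small. The document says that some therapists lead two groups and sets two as a maximum, so f = 1 is an upper bound. The bottom row of the table also needs the whole group correlation to come from the therapist and none from the group itself. At f = 0.5 and r = 0.02 to 0.05, type I error is 5.5% to 6.3% and end-of-treatment power stays above 90%. Baseline adjustment is planned but not credited in the sample size. With an assumed baseline–outcome correlation of 0.5, residual variance falls to 1 − 0.5² = 0.75 of its value, and even the bottom row gives 92.8% at end of treatment and 90.1% at six months. All of this stands, and it limits the size of the problem. It does not restore the type I error, because baseline adjustment makes the estimate more precise but leaves two groups of one therapist treated as independent. Nor does the document give a ground for taking f and r as small.

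It is also fair that the therapist variance would be poorly estimated. In a simulation with four two-group therapists per arm, the estimate was zero or negative in about 43% of runs at r = 0.02 and 30% at r = 0.05. That calls for a prespecified fallback and does not justify omitting the term.

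Three stronger readings are tempting, and the document does not support them:
- That the standard error is wrong whenever therapists differ. The group random effect covers every one-group therapist.
- That therapist variance cannot be told apart from the arm effect. With 16 groups per arm and at most two per therapist there are at least 8 therapists per arm, so it can be estimated within arm.
- That the error favours BPT. A standard error that is too small raises false positives equally in both directions.

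Which reference distribution and degrees of freedom to use with 32 groups is a separate matter, commonly left to the analysis plan, and forms no part of this point.

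**Conclusion.** The concern holds in this limited form. The plan rules out acting on a therapist effect even if its own assessment finds one. To the extent that two-group therapists induce correlation between their groups, the primary interval is too narrow and the two-sided type I error is above 5%. The size depends on two quantities the document does not give. Over r = 0.02 to 0.10, end-of-treatment type I error is 5.5% to 7.6% with half the groups sharing a therapist and 6.0% to 10.2% with all of them sharing.

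A reader might infer that the stated power is false. It is not: 94% and 91% follow from the stated inputs. They are conditional on independent groups, a condition that the section leaves unsaid. The main harm is to type I error and interval width, with loss of power second.

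**What to change.** In Statistical analysis, replace the clause that leaves therapist clustering out with a commitment along these lines: the primary continuous-outcome model will include a random effect for therapist or instructor, with therapy groups nested within it, whatever its estimated size; if the two levels cannot be separated, the therapist or instructor will be the clustering unit. The fallback has to be fixed in advance, given how weakly the variance component may be estimated. The count and ordinal models need not follow the same form.

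In Proposed sample size, state that 94% and 91% assume no correlation between groups sharing a therapist, or give power as a range over f and r as in the table. Stating how many therapists are expected to lead two groups would narrow that range.

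The cost is a slightly wider confidence interval, a weakly estimated variance component and slightly lower stated power. No new data are needed, because the leader of each group is known.

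### The one departure from missing at random that the plan names treats both arms alike, so it should not serve as the extreme case

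*Protocol article*

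**What the plan says.** All of this is in the Protocol article.

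- **Primary analysis** (Statistical analysis): "The primary analysis will be an available case analysis following intention to treat principles".
- **Sensitivity to missing data** (same section): a set of analyses is promised, extreme scenarios among them, with one offered as an example: that "those who are lost to follow up would have no improvement as result of any intervention". The reference to any intervention covers both BPT and Pilates.
- **Imputation** (same section): to be used only if enough values are missing. "We expect to use the MAR (missing at random) assumption in this imputation".
- **Expected loss** (Proposed sample size): for end of treatment, "Assuming an intra-cluster correlation coefficient for treatment group of 0.1, and 7 patients per group with analysable data at the end of treatment", out of groups of about 8. For the later time point, "At six months we expect a loss to follow-up of 31%, resulting in 5.5 individuals per group on average and an inflation factor of 1.45". Neither figure is split by arm.
- **Primary time point** (Outcome measures): end of treatment.

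**The concern.** A scenario called extreme should show whether the result survives assumptions clearly unfavourable to it. In a two-arm comparison these are usually assumptions under which missing patients do worse in one arm than in the other. Setting improvement to zero for everyone lost, in both arms, does not do this. With equal loss it dilutes the difference by a known fraction. With unequal loss it moves the difference towards the arm that lost fewer patients, whichever that is.

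At stake is how the sensitivity analysis is read. If the symmetric scenario were taken as the hardest test, a result could be called robust to informative loss without having met an arm-specific departure. The estimate and test from the primary analysis are not touched.

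**Working it through.** **Inputs from the document (Proposed sample size):** difference D = 3, SD 5, alpha 5% (taken as two-sided; not stated), intra-cluster correlation 0.1, 128 recruited per arm, 7 of about 8 per group analysable at end of treatment (implied loss 1 − 7/8 = 12.5%), and 31% loss at six months leaving 88 per arm.

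**Assumed inputs, not in the document:** mean improvement m in Pilates (1 to 5 points), gap in loss between arms (10 or 20 percentage points), and a 5-point shift (one planned SD) in lost patients.

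**1. The plan's own figures.** The unclustered size is 2 × (1.96 + 1.2816)² × 25/9 = 58.4 per arm, against the stated 58. 58 × 1.6 = 92.8, against 93. Power with 112/1.6 = 70 effective per arm is 94.4%, against 94%. With 88/1.45 = 60.7 it is 91.1%, against 91%. All are reproduced.

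**2. What the named scenario does.** Let Pilates improve by m, BPT by m + D, with losses dP and dB unrelated to outcome. With zero improvement in those lost, the difference is

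(1 − dB)(m + D) − (1 − dP)m = (1 − dB)D + m(dP − dB).

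**3. Equal loss.** The second term vanishes and the difference is (1 − d)D. A shift of δ points in lost BPT patients only, applied after imputation under missing at random, gives D − dδ.

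| | Loss 12.5% | Loss 31% |
|---|---|---|
| Named scenario | 3 × 0.875 = 2.63 | 3 × 0.69 = 2.07 |
| BPT-only shift, 5 points | 3 − 0.125 × 5 = 2.38 | 3 − 0.31 × 5 = 1.45 |

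The two coincide when δ = D. With equal loss, then, the named scenario is equivalent to a BPT-only shift of 3 points. Any larger BPT-only shift is more adverse.

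**4. Whether that could alter a conclusion.** Holding the planned standard error fixed as an approximation:

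- End of treatment: SE = √(2 × 25 × 1.6/112) = 0.85, so an estimate needs about 1.96 × 0.85 = 1.66 to reach significance. Both 2.63 and 2.38 pass.
- Six months: SE = √(2 × 25 × 1.45/88) = 0.91, threshold about 1.78. The named scenario passes (2.07) and the BPT-only shift does not (1.45). The tipping shift is about (3 − 1.78)/0.31 = 3.9 points.

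**5. Unequal loss, no true difference.** With D = 0 the scenario yields m(dP − dB). For m = 3 and a 10-point gap this is 3 × 0.10 = 0.3 points in favour of the arm with less loss. Over m from 1 to 5 and gaps of 10 to 20 points, the range is 0.1 to 1.0. A simulation (16 groups of 8 per arm, intra-cluster correlation 0.1, SD 5, loss unrelated to outcome, 4,000 runs, m = 3) gave two-sided type I error of 7.5% for losses of 26% in BPT and 36% in Pilates, and 13.2% for 21% and 41%. The available-case analysis stayed near 5%.

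**6. Unequal loss, true difference 3, m = 3.** Loss of 21% in BPT and 41% in Pilates leaves 0.79 × 6 − 0.59 × 3 = 2.97, so almost no stress. Reversing the losses leaves 0.59 × 6 − 0.79 × 3 = 1.17, which is conservative.

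**The case against.** The strongest reply is that an illustration is being read as the plan. The sentence is explicitly an example within a plural set of analyses, and the article condenses a fuller protocol. A reader might infer that no arm-specific analysis is planned; the wording does not support that. This stands, and it limits the point to the suitability of the one scenario named.

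Three other stronger readings also go too far.

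- *The scenario will create a spurious BPT benefit.* That needs higher study loss in Pilates together with non-zero improvement, and the article quantifies neither. The clause beginning "In case group dropout (as opposed to study dropout) is higher in one condition compared to the other" might be taken as a forecast of unequal loss, but it concerns attendance at the groups and expressly sets study dropout apart. The section on sample size also says that patients who leave treatment will be followed up where possible in both arms.
- *Filling in a fixed value understates the standard error.* The article states an assumption about lost patients, not how it will be implemented. Even with a fixed value, the simulation with equal 31% loss gave type I error of 4.0% (m = 3) and 5.1% (m = 5), with no sign of inflation.
- *The primary result is at risk.* At end of treatment the two approaches differ by only 0.25 points for a 3-point effect. The larger contrast is at six months. Part of the 31% may also precede randomisation, because the estimate counts dropout before treatment starts while randomisation follows the baseline assessment.

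None of this makes the symmetric scenario a bound.

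**Conclusion.** The point holds as a minor one. The only missing-not-at-random assumption named in the article is symmetric across arms, so it is neither a worst case nor reliably conservative. For a 3-point effect with equal loss, it gives about 2.6 at end of treatment and 2.1 at six months. A 5-point BPT-only shift gives about 2.4 and 1.45. With unequal loss its direction depends on which arm loses more, and the size is modest against the 3-point target: 0.3 points for the assumed 3-point improvement and 10-point gap.

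The equal-loss figures rest on the plan's own loss rates and a 5-point shift chosen for illustration. The unequal-loss figures rest wholly on assumed improvements and gaps. The primary analysis is unaffected.

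**What to change.** Keep the symmetric scenario if wanted, but do not rely on it as the extreme case. Add multiple imputation under missing at random followed by shifts varied separately by arm, for example 0 to 5 PANSS negative points worse in missing BPT patients only, in missing Pilates patients only, and in both. Report the shift at which the conclusion changes, at end of treatment and at six months. If the full analysis plan already contains such scenarios, it is enough to cite them in place of the present example.

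This needs no new data and only a little extra analysis. The cost is a few more sensitivity results to report.
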